### **10.1. Independent safety monitoring committee**

This study will include an independent safety monitoring committee which will consist of consultant cardiologist specialising in cardiac devices and electrophysiology [REDACTED] and consultant clinical oncologist specialising in the radiotherapy treatment of head and neck cancers, [REDACTED]. This committee will routinely meet after the completion of each dose of the dose escalation protocol (see figure 2.), and dose escalation will only occur once the committee is satisfied with safety. In addition, if any SAE (as defined in section 10.2) is detected during study follow up visits, this will trigger a safety committee review. No further patients will be recruited, and no further participants will receive radiotherapy pending outcome of this review.

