**6. OBJECTIVES AND OUTCOME MEASURES**

| Objectives                                                                                                                                           | Outcome Measures                                                                                                                                                                                                              | Timepoint(s) of evaluation of this outcome measure (if applicable)                                       |
|------------------------------------------------------------------------------------------------------------------------------------------------------|-------------------------------------------------------------------------------------------------------------------------------------------------------------------------------------------------------------------------------|----------------------------------------------------------------------------------------------------------|
| Primary objectives                                                                                                                            |                                                                                                                                                                                                                               |                                                                                                          |
| Assess the safety of hypofractionated radiotherapy to modify the stellate ganglia in patients with recurrent ventricular arrhythmia                  | Treatment related serious adverse events (SAEs) defined as any grade 3 toxicity requiring hospitalization or any grade 4 to 5 toxicity in the first 6 months as defined by the common terminology criteria for adverse events | During all hypofractionated radiotherapy sessions and monitoring visits up to 6 months post radiotherapy |
|                                                                                                                                                      | Treatment related side effects based on patient symptom questionnaires and clinical examination during study visits                                                                                                           | During all hypofractionated radiotherapy sessions and monitoring visits up to 6 months post radiotherapy |

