A dose escalation protocol will be used to determine the lowest radiotherapy dose that can safely achieve sympathetic downregulation. This protocol will involve 13 patients with the doses escalated as follows: The first 3 patients would be treated at 8 Gy per fraction for 3 fractions on alternate days. If no serious adverse events occur then we will increase the dose to 9 Gy per fraction for 3 fractions on alternate days in the next 3 patients, 10 Gy per fraction for the next 3 patients for 3 fractions on alternate days and 11 Gy per fraction for 3 fractions on alternate days for the final 4 patients (figure 2). There will be a minimum of 6 weeks between the last participant treated at each dose before escalation the next dose to allow for detection of adverse events at participants' 6 week follow up visit. Before each dose escalation we will have an independent safety committee review all patient data and radiotherapy doses will only be escalated if there are no safety concerns.

Our study is a safety study, and we are powered to detect serious adverse events as our primary endpoint. Serious adverse events (SAEs) defined as any related and unexpected grade 3 toxicity requiring hospitalization, grade 4 toxicity or grade 5 toxicity as defined by the common terminology criteria for adverse events.

If a serious adverse event occurs, then no further fractions would be given to that patient and the dose would be reduced by 1 Gy for all subsequent patients (up to a total of 13 patients) without further dose escalation. If an SAE occurs at the lowest radiotherapy dose (8 Gy per fraction for 3 fractions) all subsequent patients will receive treatment at the even lower dose of 7 Gy per fraction for 3 fractions, if approved by our independent safety committee. However as highlighted in section 5 we have chosen a starting dose within the safe upper limit for neuronal tissue, so we do not anticipate this. An early stopping rule will be set to halt enrolment if 4 out of the first 8 patients develop and SAE. If patients withdraw from this trial then they will be replaced, and the study will continue until 13 patients have completed the dose escalation protocol (as detailed in section 9.8). We will not recruit any extra participants into our dose escalation protocol, unless participants withdraw, in which case they will be replaced. Once 13 participants complete the dose escalation protocol no further patients will be recruited.

Figure 2.

[figure not shown]

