### Visits 4 to 6 – Hypofractionated radiotherapy to the stellate ganglia

Over the course of one-week, patients will undergo up to 3 fractions of hypofractionated radiotherapy targeted bilaterally to the lower half of the stellate ganglia and T1-2 paravertebral chain (60 minutes).

Prior to each fraction of radiotherapy blood samples (approximately 16 ml) will be taken to monitor plasma levels of NPY and other biomarkers. Routine blood tests (including renal function, full blood count and thyroid function) will also be checked prior to the first fraction of treatment. Blood samples will be labelled with the participants' study number and stored for analysis. All stored samples will be de-identified and will only be identified by a study specific participant number and will be destroyed after processing, unless participants have specifically consented to have their samples stored for use in future studies (10 minutes)

Before and after each fraction of radiotherapy a cardiovascular examination and neurological examination will be performed by one of the study doctors paying attention to signs of Horner's syndrome

(ptosis and pupil constriction) or upper limb sensory impairment. Cardiovascular observations including postural blood pressures and heart rate will be recorded, and an electrocardiogram will be performed. New postural hypotension defined as a symptomatic postural blood pressure drop of 20mmHg will be considered significant. (10 minutes each) If any serious treatment related adverse events are detected, then no further fractions of radiation will be delivered to that patient.

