## **10. SAFETY REPORTING**

This study is primarily a safety study and is specifically powered to detect SAEs (see section 11.3). The safety reporting window will be from the first fraction of radiotherapy until completion of the 6 months study follow up. A 6 months SAE reporting window is felt to be sufficient as adverse events related to cardiac sympathetic denervation should be apparent during treatment or within days, weeks or months of completion of radiotherapy if we consider trigeminal neuralgia as a parallel (78). Indeed, over the course of 6 months we will monitor any adverse events and side-effects and the expectation is that side effects will improve rather than worsen over this time period, as is observed following surgical removal of the stellate ganglia(20)

With respect to adverse events following radiotherapy, we expect to detect any dose limiting toxicity within 6 weeks of completion of radiotherapy, which is an accepted monitoring period for dose escalation trials involving radiotherapy (79). In terms of stochastic adverse effects, in the long term, ionising radiation can also cause cancer which manifests itself after many years or decades and is an accepted side-effect of the treatment. It is not likely that we would detect such adverse events even if our reporting window was extended beyond 6 months. Indeed, our study population of patients with severe heart failure and recurrent ventricular arrhythmias has a particularly poor prognosis, even despite all current available medical therapies, with mortality rates observed in excess of 50% at 5 years(67). As such late stochastic events might never become apparent.

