#### **13.3. Study Committees**

This study will include an independent safety monitoring committee which will consist of consultant cardiologist specialising in complex implantable cardiac devices and electrophysiology [REDACTED], and a consultant clinical oncologist specialising in the radiotherapy treatment of head and neck cancers [REDACTED]. This committee will routinely meet after the completion of each dose of the dose escalation protocol (see figure 2.), and dose escalation will only occur once the committee is satisfied with safety. In addition, if any SAE (as defined in section 10.2) is detected during study follow up visits, this will trigger a safety committee review. No further patients will be recruited and no further patients will receive radiotherapy pending outcome of this review.

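### The unscheduled safety review and study-wide pause are tied to SAEs found at follow-up visits, which is narrower than the protocol's own safety window

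*Protocol*

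**What the plan says.** Section 10.1 gives the safety committee two kinds of meeting: a routine one after each dose level, and an unscheduled one. The unscheduled one is worded: "if any SAE (as defined in section 10.2) is detected during study follow up visits, this will trigger a safety committee review". The consequence follows directly: "No further patients will be recruited, and no further participants will receive radiotherapy pending outcome of this review". Section 13.3 repeats the condition: "if any SAE (as defined in section 10.2) is detected during study follow up visits".

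The safety window is wider. Section 10 states: "The safety reporting window will be from the first fraction of radiotherapy until completion of the 6 months study follow up". It also expects that "adverse events related to cardiac sympathetic denervation should be apparent during treatment or within days, weeks or months of completion of radiotherapy". Appendix A schedules adverse event assessments from Visit 4, the first fraction, onwards.

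For a serious event in the treatment week, section 9.6 gives a rule at patient level: "If any serious treatment related adverse events are detected, then no further fractions of radiation will be delivered to that patient".

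**The concern.** In a dose-escalation study whose primary endpoint is safety, the independent review and the halt to further treatment should start when a serious event becomes known. Here the wording appears to leave out the treatment week, although the protocol itself expects some events then. It also appears to leave out anything learned of outside a visit, most plainly a death. At stake is whether other participants can go on being irradiated, and new ones recruited, before the committee has looked at the event.

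**Working it through.** The protocol states no figure on this point, so the check is a comparison of sections.

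1. **What counts as a follow-up visit.** The term is not defined. Section 7 speaks of the "6 week follow up visit", which is Visit 7. Section 9.6 describes patients being followed up once radiotherapy is complete, at 6 weeks, 3 months and 6 months (Visits 7 to 9). Section 6 names treatment sessions apart from later visits: "During all hypofractionated radiotherapy sessions and monitoring visits up to 6 months post radiotherapy". The most natural reading is Visits 7 to 9.

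2. **Trigger against window.**

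| Period | In the safety window (section 10)? | Meets the trigger as worded (10.1, 13.3)? |
|---|---|---|
| Visits 4 to 6 | Yes | No |
| Between visits, death | Yes | No; it cannot be found at that patient's visit |
| Between visits, non-fatal SAE | Yes | Only once seen at a later follow-up visit |
| Visits 7 to 9 | Yes | Yes |

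3. **Does a broader reading close the gap?** If every study visit counted, Visits 4 to 6 would be covered, but deaths and admissions learned of between visits would not. Section 10.3 already uses awareness as its standard: the clock for ethics committee reports starts when the Chief Investigator learns of the event.

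4. **What the other rules cover.**
   - Section 9.6 stops fractions for the affected patient after a serious treatment-related event.
   - Section 7 lowers the dose by 1 Gy per fraction for subsequent patients and bars further escalation. Its SAE definition is limited to related and unexpected toxicity: grade 3 needing hospitalisation, or grade 4 or 5. Section 10.2, on which the section 10.1 trigger rests, is wider and includes any inpatient hospitalisation.
   - Section 7 has the committee review all data before each escalation, and a step down to 7 Gy needs its approval.
   - Section 10.3 sends related and unexpected SAEs to the ethics committee within 15 working days.
   - Section 11.6 stops enrolment at 4 or more of the first 8 participants, so a single event does not activate it.

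5. **What is left.** First, a participant already mid-course is not clearly a subsequent patient under section 7; only the section 10.1 pause expressly reaches that person. Section 7 sets 6 weeks between dose levels but states no spacing within a level, so overlap is not excluded. Second, a treatment-week SAE judged unrelated, or judged expected (section 9.4.1 lists hypotension and Horner's syndrome as possible effects), may reach the committee only at the next routine dose-level meeting.

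6. **Calendar context.** Three alternate-day fractions (days 0, 2, 4) take at least 4 days, and section 9.6 allows one week. Visit 7 is 6 weeks (42 days) after completion. First fraction to Visit 7 is therefore 4 + 42 = 46 to 7 + 42 = 49 days, or 6.6 to 7.0 weeks, unless the visit is brought forward. This is the length of the stretch before the first scheduled follow-up visit. It does not estimate how long a review would be delayed.

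**The case against.** The strongest reply is that this is drafting and nobody would apply it literally. Follow-up visit is undefined, and Visits 7 to 9 are mostly called safety or monitoring visits. Sections 9.8 and 10.5 use study follow-up more loosely. The treatment week is also the most closely watched period, with cardiovascular and neurological examination before and after every fraction. An investigator who learned of a death would surely call the committee.

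Much of that stands. The intent was probably any SAE in the safety window, and nothing suggests a decision to exclude the treatment week. What does not stand is that the other rules make the trigger unnecessary: none of them provides the immediate study-wide pause, and the dose rule applies only to related and unexpected events.

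A reader might infer more: that treatment-week SAEs go unanswered, that deaths would never reach the committee, or that reviews would run weeks late. The protocol does not support these. Fractions stop and doses fall under rules that do not depend on a follow-up visit, all data come before the committee ahead of each escalation, and visits can be brought forward on clinical grounds.

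**Conclusion.** The point holds as a minor mismatch between a stated safety rule and the protocol's own safety window. Followed as written, the unscheduled review and pause miss SAEs at Visits 4 to 6 and do not start when deaths or admissions become known between visits. The treatment-week part rests on reading follow-up visits as Visits 7 to 9; the between-visit part holds on either reading.

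The remaining risk is limited to the two cases above. The protocol gives no basis for an event rate, a number of patients affected or an expected delay. The sample size, test and primary endpoint definition are not affected.

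**What to change.** In sections 10.1 and 13.3, replace the phrase limiting detection to follow-up visits with: *becomes known to the study team at any time from the first fraction of radiotherapy to the end of the 6-month follow-up*. Section 7 needs no addition, because the pause already in section 10.1 would then apply to everyone awaiting or receiving treatment.

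The cost is one phrase in two places, using the existing committee. In operation there would be a few more ad hoc reviews and short pauses, including for unrelated admissions, since section 10.2 counts any inpatient hospitalisation. A pause could also interrupt another patient's alternate-day course. Section 11.4 restricts the analysis to participants who completed bilateral treatment, so a patient who did not then finish would fall outside it. Prompt reviews would keep that risk low.

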## 5. BACKGROUND AND RATIONALE

### a) Background to the Study and Pilot Data

#### Background

Ventricular arrhythmias (VA) are a life-threatening event and are the most common cause of cardiac arrest and sudden cardiac death (SCD) (1). It is estimated that SCD accounts for up to 20% of deaths in the western world(2). Patients with structural heart disease such a heart failure with reduced ejection fraction (HFrEF) are at increased risk of SCD. There are around 900,000 people living with heart failure in the UK (3) with an estimated 200,000 new diagnoses each year(4). Despite advances in medical therapy, HFrEF is still associated with a high mortality rate, a large proportion of which is due to SCD(5).

To-date beta-blockers are the only primary prevention anti-arrhythmic drugs that are proven to reduce mortality due to VAs in heart failure patients (5, 6). Other classes of antiarrhythmic drugs lack a mortality

benefit(7-9) or even lead to excess mortality through pro-arrhythmic effects(10). However, despite optimal medical therapy including beta-blockers, the risk of arrhythmia and death in HFrEF remains high, at around 7-10% annually(9, 11). In patients at very high risk, such as those with severe heart failure or who have survived a VA event, the implantable cardioverted defibrillator (ICD) improves mortality(9) (11). While such devices are effective at treating VAs once they occur, and thus reducing mortality associated with SCD, they do not prevent the arrhythmia occurring in the first place. Patients with incessant VA's may thus experience recurrent device therapy associated with increased mortality(12) and significant impact on quality of life. Prevention of VAs is thus vital. Anti-arrhythmic drugs can reduce VA episodes but are associated with side-effects and limited efficacy(13). While catheter ablation has been shown to be effective at reducing VAs(14) a significant number of patients continue to have refractory VAs, and the main large trials of VT ablation (eg SMASH-VT, VTACH, SMS, VANISH) have failed to demonstrate a significant reduction in mortality which remains high(15-18). Few remaining options therefore exist for such patients. More recently, surgically removing the sympathetic nerves that innervate the heart via removal of the stellate ganglia (cardiac sympathetic denervation) has proven to be an effective treatment(19, 20) although surgical complication rates are high(19).

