### 8.2. Inclusion Criteria

#### General Inclusion Criteria

- Participant is willing and able to give informed consent for participation in the study.
- Male or Female, aged at least 18 years old.
- Known diagnosis of structural heart disease defined as any patient with impaired left ventricular ejection fraction (less than 55%) due to any cause including ischaemic cardiomyopathy, dilated cardiomyopathy, hypertrophic cardiomyopathy or Arrhythmogenic cardiomyopathy.
- CMR compatible ICD device implanted a minimum of 6 months ago, under follow-up at Oxford University Hospitals NHS Foundation Trust.
- Experienced more than one appropriate ICD therapy (shocks or ATP) for ventricular arrhythmia in the last 6 months
- Established on optimal guideline based medical therapy for heart failure and arrhythmia

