#### ICD interrogation and monitoring

Throughout the study duration, all patients ICDs will be monitored remotely through the pacing clinic as part of standard clinical care for these patients. Prior to patient safety visits the study team will access these records to identify any device treatments (shocks or ATP) delivered for ventricular arrhythmias and determine heart rate parameters.

Figure 3. Study flow chart

[figure not shown]

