### **10.2. Definition of Serious Adverse Events**

A serious adverse event is any untoward medical occurrence that

- results in death
- is life-threatening
- requires inpatient hospitalisation or prolongation of existing hospitalisation
- results in persistent or significant disability/incapacity
- consists of a congenital anomaly or birth defect.

Other 'important medical events' may also be considered a serious adverse event when, based upon appropriate medical judgement, the event may jeopardise the participant and may require medical or surgical intervention to prevent one of the outcomes listed above.

NOTE: The term "life-threatening" in the definition of "serious" refers to an event in which the participant was at risk of death at the time of the event; it does not refer to an event which hypothetically might have caused death if it were more severe.

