#### **11.4. Analysis populations**

All participants who completed their course of radiotherapy bilaterally to the stellate ganglia (an adverse event analysis).

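### The pause on recruitment and radiotherapy uses a wider SAE than the dose and stopping rules, and section 11.4 drops anyone whose course is cut short from the safety analysis

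*Protocol*

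**What the plan says.** Section 10.1, repeated almost word for word in section 13.3, sets the pause: "if any SAE (as defined in section 10.2) is detected during study follow up visits, this will trigger a safety committee review". The consequence follows at once: "No further patients will be recruited, and no further participants will receive radiotherapy pending outcome of this review".

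Section 10.2 defines the SAE by seriousness alone. It covers death, life-threatening events and any event that "requires inpatient hospitalisation or prolongation of existing hospitalisation", among others. It has no causality condition and no exemption for outcome events or for the underlying disease. A note limits the life-threatening limb to events in which the participant was at risk of death at the time.

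Section 9.6 (Visits 4 to 6) sets the course: "Over the course of one-week, patients will undergo up to 3 fractions of hypofractionated radiotherapy". Section 11.4 defines the only analysis population, described there as an adverse event analysis: "All participants who completed their course of radiotherapy bilaterally to the stellate ganglia".

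The population has recurrent arrhythmia by design. Section 8.2 requires that each participant has "Experienced more than one appropriate ICD therapy (shocks or ATP) for ventricular arrhythmia in the last 6 months". Section 5 opens by saying that "Ventricular arrhythmias (VA) are a life-threatening event". Under ICD interrogation and monitoring in section 9.6, staff read device records before each safety visit to "identify any device treatments (shocks or ATP) delivered for ventricular arrhythmias". The number of device-treated arrhythmias is a secondary outcome (section 6).

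**The concern.** One word, SAE, drives several rules, and it does not mean the same thing in each. The broadest meaning is attached to the rule that stops radiotherapy for everyone. Events of the underlying disease can therefore set off the pause even when nobody thinks radiotherapy caused them, and the protocol does not say how device-treated arrhythmias or disease-related admissions are to be classed for this purpose. Staff would have to choose between pausing for expected disease events and quietly not applying the written rule.

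The second problem concerns the data. The pause text does not say what happens to a participant who is between alternate-day fractions. Whatever the reason a course is cut short, section 11.4 then removes that participant from the adverse event analysis. In a 13-patient safety study, participants who received radiation would be missing from the safety result, and they would not be missing at random.

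**Working it through.** **1. The SAE behind each rule**

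| Rule | Section | Event required |
|---|---|---|
| Primary outcome | 3, 6 | treatment related, by CTCAE grade |
| Dose reduction, no further escalation | 7, Figure 2 | related and unexpected, by CTCAE grade |
| Stop a patient's own fractions | 9.6 | serious and treatment related |
| Early stopping, at least 4 of first 8 | 11.6 | related and unexpected |
| Report to the ethics committee | 10.3 | related and unexpected |
| Pause recruitment and all radiotherapy | 10.1, 13.3 | any section 10.2 SAE |

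Only the last row has no relatedness condition.

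**2. How often death alone would meet the trigger**

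The protocol states no expected number of pauses, so there is no figure to reproduce. Inputs: mortality above 50% at 5 years (sections 9.4.1 and 10), 13 participants (11.3), a 6-month safety window (10). Assumptions: constant hazard, and mortality of exactly 50%, which makes the results lower bounds under that hazard.

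- Six-month risk: 1 − 0.5^(1/10) = 0.067.
- Expected deaths: 13 × 0.067 = 0.87.
- At least one: 1 − (1 − 0.067)^13 = 0.59.
- At least two: 1 − 0.933^13 − 13 × 0.067 × 0.933^12 = 0.21.

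A death among the last participants may come when nobody is left to treat. Counting only the nine planned before the final group of four, the chance of at least one is 1 − 0.5^0.9 = 0.46.

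**3. Adding admissions and other section 10.2 SAEs**

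The protocol gives no rate. Over an assumed range for the share of participants with at least one such SAE in 6 months (binomial, n = 13):

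| Assumed share | Expected participants | At least 1 | At least 2 |
|---|---|---|---|
| 10% | 1.3 | 75% | 38% |
| 20% | 2.6 | 94% | 77% |
| 30% | 3.9 | 99% | 94% |

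**4. Chance that a pause falls inside someone else's course**

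Assume 13 courses spread evenly over the 24 months of section 8.1, four days from first to last fraction, and one detection per affected participant at the 6-week, 3-month or 6-month visit. Roughly, each pause meets another participant's course with probability 12 × 4 / 730 = 0.066. A simulation on these assumptions, which allows for detections after the last course, gives a chance of at least one hit of 13% at a 20% share and 30% at a 50% share. Over the 48 months in the synopsis, the chance per pause halves to 12 × 4 / 1460 = 0.033.

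**5. What section 11.4 does to a course that is cut short**

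A participant with a serious treatment-related event after fraction 1 or 2 receives no more fractions (sections 7 and 9.6). That participant has not completed the course and so falls outside section 11.4. The same holds for anyone whose course is broken by a pause and not finished.

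To see what one omission can do, take the one-sided test against 34% as an exact binomial test (the protocol does not name the version). With 13 analysed, P(X ≤ 1) = 0.035 and P(X ≤ 2) = 0.128, so one event passes at 0.05 and two do not. If two of 13 treated have events and one of them is dropped, the analysis sees 1 of 12, P(X ≤ 1) = 0.049, which passes. If the dropped participant is replaced and the replacement has no event, it sees 1 of 13, which also passes, although 2 of the 14 treated would not.

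**The case against.** The strongest reply is that the breadth is deliberate. The required dose has not been established, the pause lasts only until an independent committee has reviewed the event, and that committee includes an electrophysiologist and a clinical oncologist who can judge relatedness. A broad trigger for a temporary hold, with narrower triggers for changing the dose or closing enrolment, is a coherent two-tier design. A death within 6 months of a novel irradiation is a reasonable thing to review. This stands as a possible intention, but the protocol does not state it.

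Four stronger readings are tempting, and the documents do not support them.

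- **That every ICD-treated arrhythmia is a section 10.2 SAE.** Section 10.2 does not name device therapies, and its note requires risk of death at the time. A shock or an admission may well qualify; whether an episode ended by anti-tachycardia pacing does is a judgement the text leaves open. The sentence in section 5 is background, not a classification.
- **That background disease would halt the trial repeatedly.** The only rate in the protocol is mortality, which gives a 21% chance of two or more deaths. Repeated pauses become likely at a share of about 20%, which is an assumption.
- **That courses will be broken.** The halt on radiotherapy can be read as no new starts, and on the simple model a pause landing inside a course is occasional.
- **That background arrhythmias contaminate the primary result.** The primary outcome requires a treatment-related event, so an arrhythmia judged unrelated is not counted.

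**Conclusion.** The point holds as an inconsistency between rules plus a defect in the analysis population. It is not a prediction that the trial will stall. The pause uses a different SAE from the dose and stopping rules, the handling of device-treated arrhythmias and disease-related admissions is unstated, and so is the position of a participant between fractions. Under a constant hazard at the cited mortality, the chance that at least one of 13 participants dies within 6 months, whatever the cause, is about 59%; the total trigger rate cannot be derived from the protocol.

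The firmest part needs no assumed rate: section 11.4 removes every participant whose course is cut short, including one stopped for a treatment-related event. On an exact test, one such omission can turn a failed safety result into a passed one. The passages should be reconciled and section 11.4 corrected before the analysis. Whether the broad pause is the right clinical rule is not a question the documents answer.

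**What to change.** 1. Reconcile the SAE terms in sections 7, 9.6, 10.1, 10.2, 11.6 and 13.3. State which definition each rule uses, how ICD-treated arrhythmias and disease-related admissions are classified, and what the pause means for a participant mid-course. The clinical rule is for the sponsor and safety committee to set. If the broad trigger is intended, say so.
2. Change section 11.4 so that every participant who received at least one fraction is in the safety analysis under the dose received, including participants who were replaced, apart from data withdrawn under section 9.8.
3. Tabulate each participant's ICD therapies after treatment beside their own pre-treatment count, by dose level, for the committee and the final report. This is an addition: it takes no arrhythmia judged treatment related out of the primary count.

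The cost is an amendment to protocol wording and one extra table from device data that the study already collects. Sample size, visits and procedures do not change.
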